#### Interventions

The intervention is an enteric-coated oral pill containing 100 mg of ASA, administered once daily, after lunch, over 12 months. The comparator will be a placebo tablet with the same characteristics as the active pills. Both arms will have the same administration schedule and will start treatment the day after randomization (day 0).

**Figure 1 figure1:**
[figure not shown]
Illustration of the study design. Participants will be randomized in block sizes of 4, 6, and 8. Stratification factors: type 2 diabetes; platelet hyperreactivity.

#### Adherence

At every hemodialysis session, participants will receive training about the importance of taking the drug as prescribed by viewing a 10-minute educational video about medication compliance on a digital tablet.

Study patients will have monthly visits with the study team to check on treatment adherence and answer any questions. During these visits, patient compliance with treatment will be assessed by direct questioning and by counting returned tablets provided on a monthly basis. Good adherence will be defined as taking at least 80% of the prescribed daily dose and attending 100% of the visits. If a patient withdraws from the trial, the study coordinator will contact the participant to find out the reasons for withdrawal.

#### Outcomes

The primary outcome is the incidence of a composite event including all of the following: cardiac death, nonfatal myocardial infarction, nonfatal stroke, arteriovenous fistula thrombosis, and TIMI major bleeding [19] by 12 months of treatment. The secondary outcomes are effect modification of treatment efficacy by the presence of type 2 diabetes mellitus or platelet hyperreactivity and the rate of TIMI minor bleeding between treatment groups.

According to the TIMI criteria, major bleeding is defined as the presence of any intracranial bleeding (excluding microhemorrhages <10 mm evident only on gradient-echo magnetic resonance imaging), fatal bleeding (bleeding that directly results in death within 7 days), or clinically overt signs of hemorrhage associated with a drop in hemoglobin of ≥5 g/dL or a ≥15% absolute decrease in hematocrit [19]. Minor bleeding is defined as clinically overt with a hemoglobin drop of 3 to 5 g/dL [19].

The profile of platelet reactivity will be determined by multiple electrode aggregometry using a Multiplate analyzer (Dynabyte GmBH). This method was chosen because it currently is the most efficient assay used to assess platelet reactivity in humans [21]. The Multiplate will measure platelet activity (defined as aggregation capability after activation with adenosine diphosphate) as the area under the curve reported in area units multiplied by time (AU×min). Platelet hyperreactivity is defined based on the manufacturer’s recommendations and published data, with a cutoff of 50 AU×min for adenosine diphosphate–induced aggregation [22].

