### Objectives

The primary and secondary objectives of this study are to evaluate aspirin’s prophylactic efficacy and safety in patients with ESRD. This will include (1) the assessment of aspirin prophylactic efficacy for all types of thrombotic events that patients with ESRD may develop, namely nonfatal stroke, nonfatal myocardial infarction, arteriovenous fistula thrombosis, and cardiac mortality, and (2) the assessment of aspirin-related major bleeding events using Thrombolysis in Myocardial Infarction (TIMI) criteria [17-19]. The study’s secondary objectives are to test for effect modification of treatment by the presence of type 2 diabetes mellitus or platelet hyperreactivity and compare the rate of TIMI minor bleeding between treatment groups.

Our hypothesis is that aspirin is superior to placebo as prophylactic therapy for thrombotic events in patients with ESRD on hemodialysis without increasing the risk of major bleeding.

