#### Study Variables

The outcome variables are the incidence of cardiac death, nonfatal myocardial infarction, nonfatal stroke, and arteriovenous fistula thrombosis, as well as the presence or absence of bleeding and its severity based on TIMI criteria [19]. The treatment variables are the exposure to the intervention (aspirin 100 mg/d or placebo). The stratification variables are the presence versus absence of type 2 diabetes mellitus and the presence versus absence of platelet hyperreactivity.

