#### Sample Size

Sample size was calculated based on estimates for the rate of events in the primary composite outcome over 1 year: TIMI major bleeding (placebo 1% vs aspirin 2.5% [15]), cardiovascular events (placebo 3.0% vs aspirin 2.5% [10]), and fistula thrombosis (placebo 19% vs aspirin 8% [23]), for a total 1-year event rate of 23% in the placebo group and 13% in the aspirin group. A sample size of 318 patients (159 per arm) provides 80% power to detect a difference between groups of this magnitude (corresponding to an HR of 0.53) using a 2-sided log-rank test and alpha=.05 (Power Analysis and Sample Size Software version 14, NCSS LLC). The sample size for the trial was increased to 342 patients (171 per arm) to account for estimated attrition of 10%.

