#### Recruitment

The estimated hemodialysis admission rate at a large dialysis center is 50 patients per month. Therefore, we expect to include 8 to 10 patients every week, completing our recruitment goal in 9 months. We propose a recruitment period of 12 months in case enrollment is slower than expected.

Eligible patients will be identified using medical records, clinician invitation letters, and internal flyers posted in patient areas. The study team will approach eligible patients to invite them to participate in the trial. All aspects of the study will be explained and all participants who agree to participate must provide written informed consent. One venous blood sample will be collected prior to randomization in order to assess platelet reactivity profile, a stratification factor for randomization.

**Table 1 table1:** Schedule and procedures during patient visits to the participating center.

Procedure	Enrollment phase (12 months)	Experimental phase (12 months)					Follow-up (6 months)
	Preliminary visit (369 to 3 days before the experimental phase)	First medical visit (day 0)	Hemodialysis sessions (approximately every 3 days)	Every 30 days	Weeks 13, 26, 39 and 52	Hemodialysis sessions (every 30 days)	
Informed consent form	X^a^						
Physical exam/medical history and medication review	X						
Inclusion/Exclusion	X						
Collection of a blood sample^b^		X			X		
Randomization		X					
Patients’ meeting with the study team and oral training about compliance to treatment		X		X			
Provision of the necessary number of pills (on a monthly basis)		X		X			
Patients’ training focused on compliance (short educative video)			X				
Counting of returned pills				X			
Blinding assessment (questionnaire)				X			
Measurement of primary and secondary outcomes^c^ during consultations with a nephrologist and a cardiologist		X			X		
Assessment of later bleeding adverse events						X	

^a^X indicates the time at which each procedure will occur.

^b^Assessment of the hematocrit, hemoglobin concentration, and platelet hyperreactivity profile.

^c^Number of events for cardiac death, nonfatal myocardial infarction, nonfatal stroke, arteriovenous fistula thrombosis, and assessment of major and minor bleeding using the Thrombolysis in Myocardial Infarction scale.

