#### Statistical Methods

Statistical analysis will be performed including all randomized patients according to their assigned treatment group (ie, intention-to-treat). The software used will be Stata 14 (StataCorp LLC). All testing will be 2-sided with statistical significance defined as *P*<.05. The primary composite outcome (first time-to-event of thrombotic events and TIMI major bleeding) will be analyzed with Kaplan-Meier curves and a log-rank test to detect difference between the groups. Cox proportional hazards regression may be used to adjust for relevant covariates, if appropriate (eg, for any unbalanced baseline characteristics that may occur by chance). Similarly, secondary outcomes will be analyzed with Kaplan-Meier curves and log-rank tests for all events. For the secondary objectives, interaction terms will be included in the Cox models above to test for interaction between treatment status and (1) the presence of type 2 diabetes and (2) platelet hyperreactivity. The proportion of patients with TIMI minor bleeding in each group will be compared with a chi-square test. If necessary, multiple imputation will be used for missing data.

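### The primary composite has no place for a fatal ischemic stroke, although a fatal hemorrhagic stroke counts as major bleeding

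*Protocol article*

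**What the plan says.** The Outcomes section defines the primary composite as "cardiac death, nonfatal myocardial infarction, nonfatal stroke, arteriovenous fistula thrombosis, and TIMI major bleeding [19", counted over 12 months of treatment. The thrombotic part of the list recurs in four other places: the Objective in the Abstract; the Objectives section, which says cardiac mortality; Study Variables ("incidence of cardiac death, nonfatal myocardial infarction, nonfatal stroke, and arteriovenous fistula thrombosis"); and footnote c of Table 1 ("Number of events for cardiac death, nonfatal myocardial infarction, nonfatal stroke, arteriovenous fistula thrombosis").

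The Objectives section describes the efficacy aim as "the assessment of aspirin prophylactic efficacy for all types of thrombotic events that patients with ESRD may develop", and then names those same components.

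Under Outcomes, TIMI major bleeding includes "any intracranial bleeding (excluding microhemorrhages <10 mm evident only on gradient-echo magnetic resonance imaging") and "fatal bleeding (bleeding that directly results in death within 7 days").

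Statistical Methods states: "The primary composite outcome (first time-to-event of thrombotic events and TIMI major bleeding) will be analyzed with Kaplan-Meier curves and a log-rank test". It gives no rule for deaths that are not components. Sample Size plans with 1-year totals of 23% on placebo and 13% on aspirin. One contribution to these is "cardiovascular events (placebo 3.0% vs aspirin 2.5% [10"); the others are fistula thrombosis (19% and 8%) and major bleeding (1% and 2.5%).

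**The concern.** Myocardial infarction is fully covered, because a fatal infarction is a cardiac death and a nonfatal one is listed. Stroke is not. Only the nonfatal form is listed, and nothing in the article extends cardiac death to cerebrovascular death. The most severe form of one of the thrombotic outcomes that aspirin is meant to prevent thus has no component to fall under, while the fatal form of a bleed that aspirin may cause has one.

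This matters for what the result means. The composite mixes benefit and harm by design (Strengths and Limitations). Under the rule as written, preventing a nonfatal ischemic stroke counts in favor of aspirin and preventing a fatal one does not.

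The second matter is the 12-month rate named in the Abstract's Objective. The Background describes a population at high risk of death. If deaths outside the composite are treated as censored, one minus the Kaplan-Meier estimate is higher than the proportion of patients who actually have an event by 12 months.

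**Working it through.** **1. Classifying strokes by the listed components** (patient with no earlier component event)

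| Event | Component that captures it | Counted? |
|---|---|---|
| Nonfatal ischemic stroke | nonfatal stroke | yes |
| Fatal ischemic stroke | none | no |
| Nonfatal hemorrhagic stroke | nonfatal stroke; intracranial bleeding | yes |
| Fatal hemorrhagic stroke | intracranial bleeding; fatal bleeding if death is within 7 days | yes |

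The rows apply equally to both arms.

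**2. The plan's own planning figures**

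- Placebo: 1 + 3.0 + 19 = 23%. Aspirin: 2.5 + 2.5 + 8 = 13%. Both agree with Sample Size.
- HR = ln(0.87)/ln(0.77) = 0.1393/0.2614 = 0.533, which agrees with the stated 0.53.
- Expected events by 12 months in 318 patients: 159 × 0.23 + 159 × 0.13 = 36.6 + 20.7 = 57.2.
- Cardiovascular share: 159 × 0.030 + 159 × 0.025 = 4.8 + 4.0 = 8.7 events. On placebo, 19 of the 23 points are fistula thrombosis.

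**3. Size of the omission**

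The document gives no rate for fatal ischemic stroke, so a range is assumed: 0.25% to 2% a year on placebo, with a relative risk on aspirin of 0.7 or 1.0.

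| Assumed placebo rate | RR | Composite, placebo / aspirin | HR | Events in 318 |
|---|---|---|---|---|
| none added | – | 23.0% / 13.0% | 0.533 | 57.2 |
| 0.25% | 0.7 | 23.25% / 13.2% | 0.534 | 57.9 |
| 0.25% | 1.0 | 23.25% / 13.25% | 0.537 | 58.0 |
| 2% | 0.7 | 25.0% / 14.4% | 0.540 | 62.6 |
| 2% | 1.0 | 25.0% / 15.0% | 0.565 | 63.6 |

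Between about 1 and 6 events would be added. With 12 months of follow-up for each patient, Schoenfeld power at 318 patients is 66% without the addition and 62% to 68% with it. By Freedman's formula it is 64% and 60% to 66%. The change is at most about 4 points. These levels lie below the stated 80%; that is a separate matter, and only the change is used here.

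**4. Kaplan-Meier rate if other deaths are censored**

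Assumptions: constant hazards; 23% and 13% taken as the Kaplan-Meier values; other deaths independent of the event and equally frequent in both arms, at an assumed proportion q a year. With λ = 0.2614 (placebo) or 0.1393 (aspirin) and m = −ln(1 − q), the cumulative incidence at 1 year is λ/(λ + m) × [1 − exp(−(λ + m))].

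| q | m | Placebo (Kaplan-Meier 23.0%) | Aspirin (Kaplan-Meier 13.0%) | Overstatement |
|---|---|---|---|---|
| 5% | 0.0513 | 22.4% | 12.7% | 0.6 and 0.3 points |
| 10% | 0.1054 | 21.9% | 12.4% | 1.1 and 0.6 points |

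The difference between arms moves from 10.0 points to 9.8 (q = 5%) or 9.5 (q = 10%).

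**The case against.** **Effect on the result.** Fistula thrombosis dominates the composite, all cardiovascular events together are expected to number about nine, and a rule applied blind to both arms does not by itself favor either. This stands, and it limits the point to one of definition and interpretation.

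**Never counted.** A reader might infer that a fatal ischemic stroke can never count. The article does not support that. A patient with an earlier fistula thrombosis or other component is already counted in a first-event analysis. Because no time limit separates fatal from nonfatal stroke, a stroke followed later by death could also be adjudicated as nonfatal.

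**Planning rate.** A reader might infer that the cardiovascular planning rate was drawn from a wider endpoint than the composite. That is not shown. The label is a fair summary of cardiac death, infarction and stroke, and the article does not say whether the source rate includes fatal stroke.

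**Inflated rates.** A reader might infer that the reported 12-month rates will be inflated. Censoring of other deaths is an inference, and the article does not commit to reporting one minus Kaplan-Meier. The handling of deaths is also commonly left to an analysis plan, which is not shown. The Background attributes the high mortality mainly to cardiovascular events, part of which the composite already counts, and the exclusion of cancer, liver disease, AIDS and severe lung disease should reduce other deaths. This half is therefore conditional and secondary.

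None of this answers the main point. The components are fixed in five places of this document, and an analysis plan should not quietly redefine the primary endpoint.

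**Conclusion.** The point holds as a gap in the primary endpoint definition that conflicts with the article's own efficacy aim. It follows from the wording and needs no assumed rate. It does not show that the comparison is biased against aspirin or that power is materially affected: over an assumed 0.25% to 2% a year of fatal ischemic stroke, power moves by at most about 4 points. The secondary point holds only if other deaths are censored and the rates are read from Kaplan-Meier curves. The overstatement is then about 0.3 to 1.1 points, for assumed other deaths of 5% to 10% a year under constant hazards. The definition should be corrected before the trial is registered and starts.

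**What to change.** In the Abstract's Objective, Objectives, Outcomes, Study Variables and footnote c of Table 1, replace cardiac death (cardiac mortality in Objectives) with cardiovascular death, including fatal stroke. The narrower alternative is to keep cardiac death and list fatal or nonfatal stroke. With either wording, whether a stroke counts no longer depends on the unstated boundary between fatal and nonfatal.

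In Statistical Methods, state how deaths outside the composite are handled. Keep the log-rank test as the comparison, report 12-month cumulative incidence (Aalen-Johansen) with other death as a competing event, and tabulate all deaths by arm.

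The cost is small but not nil. According to Results, the trial is not yet registered and has no start date, so the wording can still change freely, and one estimator is added. However, Outcomes Assessment provides only for adjudication of study outcomes and end points by a nephrologist, a cardiologist and a nurse. It does not say that the cause of every death is classified, so the panel would have to classify cerebrovascular deaths as well, and all deaths would have to be recorded.

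### A fatal ischemic stroke fits no component of the primary composite, although the same stroke counts when the patient survives

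*Protocol article*

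**What the plan says.** The Outcomes section of the protocol article defines the primary outcome as a composite of "cardiac death, nonfatal myocardial infarction, nonfatal stroke, arteriovenous fistula thrombosis, and TIMI major bleeding" by 12 months. The Introduction's Objectives section gives the thrombotic part as "namely nonfatal stroke, nonfatal myocardial infarction, arteriovenous fistula thrombosis, and cardiac mortality". Study Variables repeats it: "The outcome variables are the incidence of cardiac death, nonfatal myocardial infarction, nonfatal stroke, and arteriovenous fistula thrombosis". Footnote c of Table 1 has it again: "Number of events for cardiac death, nonfatal myocardial infarction, nonfatal stroke, arteriovenous fistula thrombosis". The Objective in the Abstract uses the same four thrombotic terms.

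The TIMI definition in Outcomes brings in some further deaths. Major bleeding covers "the presence of any intracranial bleeding", apart from small microhemorrhages seen on one type of MRI only, and also bleeding that leads directly to death within 7 days.

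Statistical Methods analyzes the time to the first component event with Kaplan-Meier curves and a log-rank test. It gives no rule for deaths that are not components.

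**The concern.** A composite of this kind should not score the worse outcome of an event more favorably than the milder one. Here stroke enters only if nonfatal, and death enters only if it is cardiac or due to bleeding. Ischemic stroke, which aspirin is meant to prevent, counts when survived and drops out when it kills. Hemorrhagic stroke, the harm feared from aspirin, counts either way. Two equally fatal strokes are therefore scored by mechanism.

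The validity of the endpoint is at stake. Event status for an ischemic stroke depends on what happens to the patient afterward. If treatment turned a fatal ischemic stroke into a survived one, the treated arm would gain an event. A competing-risk method for other deaths would not repair this, because the stroke would still not be an event.

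**Working it through.** **Step 1: set each event against the listed components.**

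| Event | Component that catches it | Counted |
|---|---|---|
| Infarction, survived | nonfatal infarction | yes |
| Infarction, fatal | cardiac death | yes |
| Hemorrhagic stroke, survived | TIMI major bleeding (intracranial); also nonfatal stroke | yes |
| Hemorrhagic stroke, fatal | TIMI major bleeding (intracranial or fatal) | yes |
| Ischemic stroke, survived | nonfatal stroke | yes |
| Ischemic stroke, fatal, no intracranial bleeding | none | **no** |

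All five places that define the thrombotic outcome give the same list, so it is not a slip in one section. No other section adds fatal stroke, vascular death or all-cause death.

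**Step 2: carry this into the analysis.** In a time-to-first-event analysis with Kaplan-Meier and log-rank, a death that is not a component ends follow-up without an event. This is inferred from the method named; the article does not state it. A patient who already had, say, a fistula thrombosis is counted from that earlier event and is unaffected.

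**Step 3: the plan's own figures (Sample Size).**
- Placebo: 1 + 3.0 + 19 = 23%. Aspirin: 2.5 + 2.5 + 8 = 13%. Both match the stated totals.
- HR = ln(1 − 0.13) / ln(1 − 0.23) = 0.533, which matches the stated 0.53.
- Fistula thrombosis supplies 19 of the 23 points in placebo and 8 of the 13 in aspirin.
- Expected cardiovascular events per arm of 171: 171 × 0.030 = 5.13 and 171 × 0.025 = 4.28.

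**Step 4: number of patients uncounted.** The article gives no rate for fatal ischemic stroke. Assume that such strokes make up 5% to 20% of cardiovascular events.
- At the placebo rate: 5.13 × 0.05 = 0.26 to 5.13 × 0.20 = 1.03 patients.
- At the aspirin rate: 4.28 × 0.05 = 0.21 to 4.28 × 0.20 = 0.86 patients.

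**Step 5: effect on the comparison.** As a separate and wider assumption, let fatal ischemic stroke occur in r = 0.25% to 2% of placebo patients per year, with an aspirin relative risk RR of 0.67 to 1.0. With 159 per arm:
- Added events = 159 × r × (1 + RR), from 159 × 0.0025 × 1.67 = 0.66 to 159 × 0.02 × 2 = 6.36.
- HR = ln(1 − 0.13 − r·RR) / ln(1 − 0.23 − r), which moves from 0.533 to between 0.534 (r = 0.25%, RR 0.67) and 0.565 (r = 2%, RR 1.0).
- Power at 318 patients and 12 months, as listed: 318 × 0.18 = 57.2 events and Φ(√57.2 × |ln 0.533| / 2 − 1.96) = 66% by Schoenfeld's formula. By Freedman's formula it is 64%.
- Power with fatal ischemic stroke counted: 62% to 69% (Schoenfeld) or 60% to 66% (Freedman).

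Only the shift matters here, and it is a few points in either direction. That the starting value lies below the planned 80% is a separate question about the sample size calculation and does not bear on this point.

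**The case against.** The strongest reply is that this is a deliberate and consistent endpoint, that operational definitions belong in the full protocol or an adjudication charter, and that the numbers are tiny. Much of that stands. Neither *nonfatal* nor *cardiac death* is defined, and there is no survival window, so the blinded adjudicators might score a stroke with delayed death as a stroke at onset. The gap would then be narrower. It would not close, because a stroke that kills promptly cannot be called nonfatal on any ordinary reading. If event status rests on an unstated survival rule, that too should be settled in the definition.

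A reader might infer more than the article supports:

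- **A contradiction with the Objectives.** The promise there to cover all types of thrombotic events is followed at once by "namely nonfatal stroke, nonfatal myocardial infarction, arteriovenous fistula thrombosis, and cardiac mortality". The phrase is defined by the same list, so the sections agree.
- **A stated censoring rule.** Statistical Methods has none.
- **The same asymmetry for other fatal noncardiac thrombotic events.** Pulmonary embolism, for example, is not a component when survived either, so its fatal form does not score better. The asymmetry is confined to ischemic stroke.
- **A mismatch with Sample Size.** *Cardiovascular events* there is a label for a rate from a cited trial. What that trial counted cannot be seen from the article.
- **A shown shift by aspirin between fatal and survived strokes.** Nothing in the article suggests one. The wrong-way movement is a property of the definition, not a predicted result.

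**Conclusion.** The gap is real: by the listed components, a fatal ischemic stroke without intracranial bleeding is not a primary event, while a survived one is. Its expected size is small, about 0.3 to 1 patient per arm of 171 at the planned 3% rate, on the assumed 5% to 20% share. Hazard ratio and power barely move under the rates tried.

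This is therefore a validity defect and not a power problem. It is also not shown to be large for the cardiovascular part of the composite. On a matched base the uncounted fraction is simply the assumed 5% to 20%, and the case fatality needed to narrow that range is not in the article. The point is still worth acting on. Strengths and Limitations says the components will be individualized in the secondary analysis, and only about 5 against 4 cardiovascular events per arm are expected there.

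**What to change.** In the Abstract's Objective, the Introduction's Objectives, Outcomes, Study Variables and footnote c of Table 1, replace *nonfatal stroke* by *stroke, fatal or nonfatal*. State that the event is timed at stroke onset whatever the later outcome, and that the existing blinded team adjudicates it.

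This closes the whole of the gap shown here. Replacing cardiac death by a wider cardiovascular death would enlarge the endpoint beyond that gap; it is a separate and debatable choice.

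The cost is low. Outcomes Assessment already has the team review records and adjudicate endpoints, so no new visits, staff or data sources are needed. The Results section says the protocol has still to be submitted for ethics review and registered. The one small follow-on task is to check the 3.0% and 2.5% cardiovascular rates in Sample Size against the revised definition.

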## Abstract

**Background:**

End-stage renal disease (ESRD) is the last stage of chronic kidney disease, mainly caused by type 2 diabetes mellitus and characterized by an increased mortality risk related to cardiovascular disease. Low-dose aspirin (acetylsalicylic acid or ASA) seems to effectively prevent cardiovascular events in patients with ESRD. However, the number of interventional studies in this population remains limited and the mechanisms of aspirin-related bleeding remain poorly understood. Aspirin’s efficacy and safety may be modified by the presence of type 2 diabetes mellitus or platelet hyperreactivity.

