**Objective:**

The overall objective of this protocol is to (1) evaluate aspirin’s safety and efficacy in reducing the risk of thrombotic events in patients with ESRD on hemodialysis and (2) examine whether aspirin’s efficacy is modified by the presence of type 2 diabetes mellitus or platelet hyperreactivity. Specifically, the primary objective is to compare the 12-month rate of any thrombotic event (cardiac death, nonfatal myocardial infarction, nonfatal stroke, arteriovenous fistula thrombosis) and Thrombolysis in Myocardial Infarction (TIMI) major bleeding in patients treated with aspirin compared to those on placebo. Secondary objectives are to test for effect modification of treatment by the presence of type 2 diabetes mellitus or platelet hyperreactivity and compare the rate of TIMI minor bleeding between treatment groups.

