**Conclusions:**

We provide a protocol for a randomized controlled trial to evaluate the safety and efficacy of treatment with aspirin to reduce the risk of thrombotic events. In addition, such a study would further our understanding of the mechanism of aspirin-related bleeding and help identify subgroups of best-responders and patients with a higher risk of adverse events.

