However, there is a lack of information about the prophylactic efficacy of aspirin for all types of thrombotic events that patients with ESRD may develop. There is also a gap of knowledge concerning the safety profile of aspirin in patients with ESRD. Concerning the risk of aspirin-related bleeding, there is some discrepancy between the results of observational and interventional studies, as an increased risk of bleeding has been reported in some observational studies [13,14]. However, interventional studies of patients with ESRD have found that low doses of aspirin are not associated with an increased risk of major bleeding in dialysis patients, despite an apparent increased risk of minor bleeding (eg, gastrointestinal bleeding) [10,15]. This discrepancy highlights the fact that the mechanism of aspirin-related bleeding events is not yet fully understood. Some authors have suggested that the prophylactic efficacy of aspirin and risk of bleeding related to this drug may be influenced by a phenomenon of platelet hyperreactivity [16]. However, further research is necessary to establish the real impact of platelet hyperreactivity on aspirin’s safety profile in patients with ESRD.

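### The protocol raises modification of aspirin's safety but specifies no bleeding-specific effect-modification analysis, and the planned interaction rests on a composite that cannot isolate bleeding

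*Protocol article*

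**What the plan says.** **Where safety modification is raised**

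- Abstract, Background: aspirin's "efficacy and safety may be modified by the presence of type 2 diabetes mellitus or platelet hyperreactivity". Both modifiers are tied to safety here.
- Background and Rationale: the text ends on "further research is necessary to establish the real impact of platelet hyperreactivity on aspirin’s safety profile in patients with ESRD". Diabetes is not named at this point.
- Abstract, Conclusions: the study would "help identify subgroups of best-responders and patients with a higher risk of adverse events".

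**How effect modification is then defined**

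- Abstract, Objective, overall aim (2): whether aspirin's "efficacy is modified by the presence of type 2 diabetes mellitus or platelet hyperreactivity".
- Objectives: "test for effect modification of treatment by the presence of type 2 diabetes mellitus or platelet hyperreactivity", with no limit to efficacy. The secondary objectives in the abstract use the same unrestricted form.
- Outcomes: "The secondary outcomes are effect modification of treatment efficacy by the presence of type 2 diabetes mellitus or platelet hyperreactivity".

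**How it is analysed**

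- Statistical Methods: "interaction terms will be included in the Cox models above", for treatment by diabetes and treatment by hyperreactivity. The Cox regression mentioned before that sentence follows the description of the primary composite, whose first events include both thrombosis and TIMI major bleeding.
- TIMI minor bleeding gets a chi-square comparison of the arms, and secondary outcomes get Kaplan-Meier curves and log-rank tests. None of these carries an interaction term.
- Strengths and Limitations says that the components of the composite are looked at individually in secondary analysis, without mentioning effect modification by component.

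**The concern.** The protocol poses a two-sided question: do these baseline characteristics change aspirin's benefit, and do they change its bleeding risk? The secondary outcome takes up only the first side by name. The one model that carries the interaction terms combines the two.

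This matters because the components are assumed to move in opposite directions on aspirin: thrombosis falls and major bleeding rises. An interaction on the composite is a net effect. If one subgroup bleeds more on aspirin, its composite hazard ratio moves towards 1, and under the Outcomes wording that would be reported as reduced efficacy. A safety signal would carry the wrong label, and the abstract's statement about patients at higher risk of adverse events would have no analysis behind it. Minor bleeding, for which Background and Rationale reports an apparent increase in interventional studies, enters no interaction at all.

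**Working it through.** **Inputs (Sample Size section, 1-year rates, placebo vs aspirin).** TIMI major bleeding 1% vs 2.5%; cardiovascular events 3.0% vs 2.5%; fistula thrombosis 19% vs 8%; 171 patients per arm. Like the plan, I add the components as if they did not overlap.

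**1. The plan's own composite figures**

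- Placebo: 1 + 3 + 19 = 23%. Aspirin: 2.5 + 2.5 + 8 = 13%. Both match.
- HR = ln(1 − 0.13) / ln(1 − 0.23) = ln(0.87) / ln(0.77) = 0.533. This matches the stated 0.53.

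**2. Share of bleeding in the composite**

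- Composite events: 171 × (0.23 + 0.13) = 61.6.
- Major bleeds: 171 × 0.01 = 1.7 on placebo and 171 × 0.025 = 4.3 on aspirin, about 6.0 in all.
- Share: 3.5 / 36 = 9.7%. Fistula thrombosis is 27 / 36 = 75% and cardiovascular events are 5.5 / 36 = 15%, together about 90%.
- By arm, bleeding is 1 / 23 = 4% of placebo events and 2.5 / 13 = 19% of aspirin events.

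**3. What a bleeding excess in one subgroup does to the composite (illustration; the 5% is my assumption)**

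- Suppose the aspirin major-bleeding rate in one subgroup is 5% instead of 2.5%, with everything else as planned. Its aspirin composite is 13 + 2.5 = 15.5%.
- HR = ln(0.845) / ln(0.77) = 0.64, against 0.53 in the other subgroup: a ratio of about 1.21.
- Precision of the composite interaction, using Var(log ratio of HRs) = 4/D₁ + 4/D₂ and assuming a 50/50 subgroup split (the documents give no prevalence): D₁ = D₂ = 30.8, variance 0.26, standard error 0.51. The ratio detectable with 80% power is exp(0.51 × 2.80) = 4.2.
- A doubling of major bleeding in a subgroup would therefore appear as a modest shift towards weaker benefit, far below what the composite interaction can detect and not recognisable as bleeding.

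**4. What a test on major bleeding alone could deliver**

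Same formula with about 6.0 events; power = Φ(ln R / √Var − 1.96).

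| Assumed split | R = 2 | R = 4 | R = 10 | R for 80% power |
|---|---|---|---|---|
| 50/50 | 6% | 13% | 29% | about 98 |
| 30/70 | 6% | 12% | 25% | about 148 |

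For 50/50, Var = 8 / 2.99 = 2.67 and √Var = 1.64. The formula takes events as evenly divided between arms. With the planned 1.7 to 4.3 split, Var is 2 × (1/0.855 + 1/2.14) = 3.27, so the table is optimistic. The minor-bleeding rate is not given, so the gain from pooling major and minor bleeds cannot be calculated.

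**The case against.** A reader might infer that effect modification is tested for efficacy only and that nothing planned touches the safety side. The document does not support that, for four reasons.

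- The composite contains TIMI major bleeding, so the planned interaction is a net-effect test and not a pure efficacy test.
- The Objectives section and the abstract's secondary objectives speak of modification of treatment without the efficacy limit, so the wording is inconsistent and not uniformly narrow.
- Strengths and Limitations says components are analysed individually, and Statistical Methods refers to Cox models in the plural. Whether that plural reaches component models is left open.
- The rationale is not about bleeding alone: the abstract's conclusion also names best responders, and Background and Rationale ties only hyperreactivity to the safety gap.

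Two further points can be made for the protocol. Its claims are hedged, and with about 6 major bleeds a formal bleeding interaction has almost no power, so leaving it out is defensible. Safety summaries by stratum are also commonly left to an SAP, which is not shown here.

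The first four points stand and set the limits of the finding. The power argument also stands, but it argues for estimates in place of tests and for a more modest abstract; it does not justify labelling a mixed interaction as efficacy. The SAP argument does not dispose of the point: the Outcomes section fixes the scope in words that differ from the Objectives, and an SAP written from it would inherit the narrower version.

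**Conclusion.** The point holds as a gap between stated aims and specified analysis. The protocol raises modification of safety (by hyperreactivity in two places, by diabetes in one) and speaks of finding patients at higher risk of adverse events, but it specifies no effect-modification analysis in which bleeding alone is the outcome. The composite interaction includes major bleeding at about 9.7% of expected events and cannot separate it from thrombosis at about 90%.

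The shares rest on the plan's assumed rates and on non-overlapping components. The illustration and the power figures also rest on assumed subgroup splits and an assumed subgroup bleeding rate. The primary comparison of aspirin with placebo is not affected. The trial cannot settle the bleeding question at this size whatever is added; what can be corrected is the labelling, the separation of the components, and the strength of the abstract's claim.

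**What to change.** 1. Use one wording, effect modification of efficacy and of bleeding, in the abstract's Objective, in Objectives, in Outcomes and in Statistical Methods. State which outcomes carry the interaction terms.
2. Report the treatment-by-factor interaction for the thrombotic components separately from bleeding, beside the composite interaction.
3. For TIMI major bleeding, and for first TIMI major-or-minor bleeding (to be defined as an endpoint), give counts by arm and arm differences or ratios with 95% CIs within each diabetes stratum and each baseline hyperreactivity stratum. Use the pre-randomisation platelet value. Add a treatment-by-factor term, one factor at a time, only if the number of events allows it; a model with both factors and both interactions asks too much of so few bleeds.
4. Label these bleeding analyses exploratory, and word the abstract's statement on higher-risk patients as hypothesis-generating.

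**Cost.** No new data or patients: bleeding severity is already a study variable assessed at the scheduled visits, and both modifiers are stratification factors. The price is some rewording, a small table, a few more exploratory comparisons and wide intervals.
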